Some children still require additional surgical intervention due to remaining velopharyngeal insufficiency (VPI) after primary palatoplasty. VPI is an anatomical deficiency where the velopharyngeal port cannot adequately close to fully separate the oral and nasal cavities during speech and/or swallowing. VPI results in hypernasality, nasal air emission, and/or weak pressure consonants. Children with VPI are also at greater risk of compensatory articulation errors, which are abnormal, learned sound substitutions [8]. All these speech issues impact a person’s ability to communicate effectively. Rates of VPI range widely among hospitals, regions, and countries between 13% and 40% [9,10]. Inability of the initial palate repair surgery to address VPI places children at risk of long-term psychosocial challenges and increases the likelihood of additional costly interventions [11-13]. Even children with otherwise successful repairs often require speech therapy, with 34% to 68% exhibiting cleft speech characteristics [14-16].

Despite advances in surgical training and multidisciplinary cleft care, the incidence of speech disorders after repair has remained high for decades [17]. The timing and technique of primary palatoplasty have been shown to influence surgical outcomes [18]; however, these do not fully explain why some children continue to experience speech difficulties. Earlier repairs tend to result in reduced hypernasality and improved consonant production [14,19], but not all studies agree, with some reporting no clear age effect in secondary VPI surgery [3]. Recent prospective evidence further supports an association between timing and early speech sound development, particularly oral stop consonant production. A recent study of 113 infants with repaired cleft palate revealed that at least one oral stop was evident in the consonant inventory for 84% of children at 16 months, 71% produced 2 or more different stops, and only 7% produced all 6 stop consonants [20]. This represents a gap in the literature supporting early surgical and speech outcomes for children with cleft palate.

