### Surgical Considerations

Participants will undergo primary palatoplasty within a typical early palate repair window prior to 15 months [38]. Two standard surgical approaches will be evaluated: IVV and Furlow DOZ. These 2 procedures are commonly used for primary palatoplasty at the study site. Due to the observational nature of this study, no standardization or changes to the surgeons’ procedures will take place; however, individual variability will be accounted for by recording the operating surgeon of each participant and controlling for any significant differences between surgeons in the analysis. Both procedures aim to restore the LVP “sling” to its intended anatomical position in the posterior velum but differ in technique. IVV reorients the muscle bundles end to end without overlap and closes the mucosa with a straight-line suture. DOZ repositions the LVP muscle via opposing Z-shaped incisions, lengthening the velum and creating overlap of the muscle bundles. All surgeries will be performed at a single institution by 1 of 5 operating surgeons. Procedure selection and the use of tissue adjuncts will be determined intraoperatively based on the surgeon’s clinical expertise, which may include a perceptual assessment of the amount of palatal tissue and/or tension upon closure of the cleft defect; no randomization will be performed. Tissue adjuncts, in this context, refer to flaps or grafts added to the palate from an alternate location in the mouth (eg, buccal fat pad flap or buccal myomucosal flap).

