**Figure 1 figure1:**
[figure not shown]
Participant-level timeline for multimodal data collection throughout the study. ASQ-3: Ages and Stages Questionnaire, Third Edition; CDI: Communicative Development Inventories; MRI: magnetic resonance imaging.

At both time points, caregivers will also complete an at-home speech recording using a LENA digital language processor (LENA Foundation) worn in a custom vest, along with a structured book reading task to capture 2 to 4 hours of the child’s vocalizations and target words. Audio files will be analyzed using modified naturalistic listening in real time (NLRT) [20,40,41]. Per the NLRT protocol, consonants will be included in the analysis only if they are produced at least twice across the sampled segments. Reflexive vocalizations will be excluded, whereas meaningful productions, including whispered or sung sounds, will be included. The primary outcome measure is consonant inventory size, defined as the total number of distinct consonants meeting the inclusion criterion across the full analyzed sample.

At both time points, caregivers will complete an intake form, the Ages and Stages Questionnaire, Third Edition [42], and the MacArthur-Bates Communicative Development Inventories [43]. Hearing-related data will be taken from the participants’ medical charts from birth up to the 18-month time point to characterize developmental, communicative, and middle-ear status alongside MRI and speech data (see Textbox 1 for a summary of participant data collected at each visit). Hearing data may include tympanometry, otitis media, and newborn hearing screening results, as available. Standardized procedures for MRI acquisition and speech data collection will ensure reliability and minimize the burden on participants and caregivers. These time points are supported by prior research demonstrating that velopharyngeal closure and early speech production are measurable in infants and toddlers with and without cleft palate. Specifically, velopharyngeal closure is largely complete by 19 months [34], some children with repaired cleft palate achieve consistent closure for stop consonants by 14 months [35], and modified NLRT provides reliable assessment of early consonant production as early as 16 months [40].

Participant data collected after enrollment and updated for each visit.

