### Evaluation Outcomes

The primary outcomes correspond to the 2 study aims. For aim 1, the primary outcome is the type of surgical procedure performed (IVV or DOZ with or without adjunct tissue use) predicted by preoperative anatomical variables, namely, cleft width and LVP muscle length. For aim 2, the primary outcome is the diversity of oral stop consonants produced at 18 months, serving as a functional measure of velopharyngeal competence. Secondary outcomes include additional anatomical measures (effective velar length, effective velopharyngeal ratio, and LVP muscle continuity) and developmental and language scores. Anatomical variable definitions are outlined in Table 1. Exploratory tertiary outcomes will examine modifiers of anatomy and speech, including sex, demographic characteristics, tympanometry results, and other developmental assessments. Missing data will be imputed (when appropriate) or addressed using pairwise deletion. Additionally, data may be analyzed cross-sectionally to meet the study aims.

**Table 1 table1:** Anatomical variables and corresponding definitions as obtained from magnetic resonance imaging for aims 1 and 2.

Variable	Definition
Cleft width	Distance between the lateral margins of the cleft at the widest point
Effective VP^a^ ratio	Effective velar length/pharyngeal depth
Effective velar length	Length of the velum from the posterior hard palate to the LVP^b^ muscle
LVP muscle angle of origin	Interior angle created by the lines drawn to measure distance between the origin points and LVP muscle length
LVP muscle continuity	Whether the LVP muscle is continuous through the midline (yes or no)
LVP muscle length	Length of the LVP muscle along one side from origin to insertion
Origin-origin distance	Distance between the points of origin of the LVP muscle
Pharyngeal depth	Distance from the posterior hard palate to the posterior pharyngeal wall at the palatal plane
VP ratio	Total velar length/pharyngeal depth
Velar insertion distance	Distance between the locations where the bilateral LVP muscle bundles insert into the body of the velum (ie, repaired velar width)
Velar length	Length of the velum from the posterior hard palate to the tip of the uvula
Velar thickness	Distance from the velar knee to the velar dimple

^a^VP: velopharyngeal.

^b^LVP: levator veli palatini.

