### Statistical Analysis

All participants with data at the relevant time points will be included in each analysis. The primary outcome will be evaluated using binomial logistic regression to determine how preoperative anatomical variables predict surgical procedure selection, controlling for sex, race, and cleft type. Principal component analysis may be applied to reduce dimensionality among anatomical predictors. The secondary outcome will be assessed using a 2-way analysis of covariance examining the effects of surgical type and number of oral stops on postsurgical anatomical measures, controlling for sex, cleft type, and developmental and language scores.

To ensure scientific rigor, intrarater and interrater reliability will be calculated for both MRI and speech measures. Independent raters will measure MRI scans and consonant productions following completion of a structured reliability training protocol to enhance measurement accuracy and precision. This training will consist of a guided review of the velopharyngeal MRI and speech literature, a detailed study of relevant cleft MRI anatomy and speech characteristics, and repeated practice measurements of both typical children and those with cleft palate until a predetermined level of agreement is reached. Each measurement training cycle will be followed by discussion-based debriefing and troubleshooting. The primary rater will measure all samples, whereas a second rater will measure a randomly selected 10% of the samples to calculate interrater reliability. The primary rater will rerate a random selection of 10% of the samples to calculate intrarater reliability.

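### The Aim 2 model adjusts for developmental and language scores that are also listed as outcomes, without saying from which visit, and it leaves out age at repair

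*Protocol article*

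**What the plan says.** The Statistical Analysis section sets Aim 2 up as a "2-way analysis of covariance examining the effects of surgical type and number of oral stops on postsurgical anatomical measures". Anatomy is therefore the dependent variable, and surgical type and number of stops are the explanatory terms. The covariates are named in the rest of that sentence, where the scores appear: "controlling for sex, cleft type, and developmental and language scores".

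Evaluation Outcomes gives the scores another role: "Secondary outcomes include additional anatomical measures (effective velar length, effective velopharyngeal ratio, and LVP muscle continuity) and developmental and language scores". The same section states: "For aim 2, the primary outcome is the diversity of oral stop consonants produced at 18 months".

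Study Design and Data Collection has the questionnaires completed twice: "At both time points, caregivers will complete an intake form, the Ages and Stages Questionnaire, Third Edition", together with the MacArthur-Bates inventories. Speech is also recorded twice: "At both time points, caregivers will also complete an at-home speech recording". Statistical Analysis does not say which visit's scores enter the model.

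On timing, the Background says: "Recent prospective evidence further supports an association between timing and early speech sound development, particularly oral stop consonant production". Surgical Considerations allows a range of ages: "Participants will undergo primary palatoplasty within a typical early palate repair window prior to 15 months". Textbox 1 records the date of repair. Neither age at repair nor time since repair is in the printed covariate list.

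**The concern.** Two features of the covariate list stand out.

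First, a variable that the plan treats as an outcome is also held constant. Language and development at 18 months may partly reflect the speech output under study; Textbox 1 itself files both instruments under speech information. Conditioning on a consequence of speech takes away information about the anatomy-speech link. With about 27 to 30 evaluable infants there is little to spare.

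Second, the plan's own rationale names repair timing as related to oral stops, and the eligibility limit lets it vary, yet the model ignores it. If repair age also relates to postsurgical anatomy, part of the anatomy-stops association would be a timing effect.

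A related weakness touches the procedure term. Surgical Considerations says that procedure is chosen in theatre, partly on perceived tissue and tension, and Aim 1 expects cleft width to predict that choice. The Aim 2 hypothesis says stop diversity is not related to procedure type. That comparison is hard to read without any measure of presurgical width.

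**Working it through.** The plan gives no alpha, power, effect size or correlation for Aim 2, so there is no figure to reproduce. The correlations below are assumptions, used to show size and direction.

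**Number of infants.** Target 30; 39 enrolled at 30% attrition leaves 39 × 0.70 = 27.3, so about 27.

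**18-month scores as a consequence of speech.** Let A be anatomy, S stops and L the score. Assume corr(A,S) = 0.50 and corr(S,L) = r, with L depending on A only through S, so corr(A,L) = 0.5r.

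- Slope of A on S given L (the printed direction): (0.5 − 0.5r²)/(1 − r²) = 0.50 for any r. It does not change.
- Its standard error is multiplied by 1/√(1 − r²): 1.25 at r = 0.6 and 1.40 at r = 0.7.
- Partial correlation: 0.5√(1 − r²)/√(1 − 0.25r²). At r = 0.6, 0.400/0.954 = 0.42. At r = 0.7, 0.357/0.937 = 0.38.
- Approximate power, Fisher z, two-sided 5% (assumed), n = 27, four other covariates in each case, so √(27 − 3 − 4) = 4.472:

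| Correlation | Fisher z | z × 4.472 − 1.96 | Power |
|---|---|---|---|
| 0.50 (no score) | 0.549 | 0.497 | 0.69 |
| 0.42 (r = 0.6) | 0.447 | 0.038 | 0.52 |
| 0.38 (r = 0.7) | 0.401 | −0.165 | 0.43 |

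A simulation starting from a true correlation of 0.40 behaves alike: with r = 0.3, 0.5 and 0.7 the partial correlation falls to 0.38, 0.35 and 0.30, and the slope of A on S stays at 0.40.

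**Other causal structures.** If L is a common cause of A and S and there is no true link, the unadjusted correlation is spurious: 0.3 × 0.3 = 0.09 or 0.5 × 0.5 = 0.25. Adjustment brings it to 0.

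**Time since repair.** Repair by 15 months with assessment at about 18 months gives 18 − 15 = 3 months. The presurgical MRI is placed at about 10 to 12 months, within 2 weeks before surgery, so the early end is about 18 − 10 = 8 months. The range is about 3 to 8 months.

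**Omitting age at repair.** With no true A-S link, the spurious correlation is the product of age at repair's correlations with A and with S:

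| With A | With S | Spurious correlation |
|---|---|---|
| 0 | 0.2 or 0.4 | 0 |
| 0.2 | 0.2 | 0.04 |
| 0.2 | 0.4 | 0.08 |
| 0.4 | 0.4 | 0.16 |

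Adjusting for age at repair returns each to 0.

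**Degrees of freedom.** Count the intercept, procedure, stops (linear), their interaction, sex, cleft type (1 or 2) and two scores (one term each, assumed): 8 or 9 parameters. That leaves 18-19 residual degrees of freedom at n = 27 and 21-22 at n = 30.

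**The case against.** The strongest reply is that no bias has been shown, and much of it stands. Both rounds of scores are collected, so the plan may already intend the presurgical ones, which are proper baseline covariates. Development may influence both anatomy and speech, in which case adjustment is right. Omitting repair age confounds the association only if repair age also relates to postsurgical anatomy. The document does not state this; the nearest it comes is the Background remark that repair timing may bear on velopharyngeal outcomes and facial growth. The Background also notes that studies disagree on an age effect for secondary surgery.

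A reader might infer that the planned slope is pulled toward zero by 30 to 42%. Those figures, 0.50 to 0.35-0.29 from (0.5 − 0.5r²)/(1 − 0.25r²), belong to stops regressed on anatomy. The printed model runs the other way, and there the slope holds while precision falls.

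A reader might also infer a threefold spread in time since repair, 3 to 9 months. The 9-month lower limit is general US practice from the Background, not a study criterion.

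Nor does an association at 18 months require a presurgical consonant inventory. Cleft width in the main model is debatable: cleft type is already adjusted for, and width is expected to track procedure, which costs precision in so small a sample.

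The study is also a pilot, and the article is condensed. That lowers the stakes, but the point concerns a covariate list that is printed and a double role that is printed. The exploratory modifier analyses do not name age at repair.

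**Conclusion.** The point holds as an ambiguity and an omission that can weaken or confound the Aim 2 result, not as a demonstrated bias. The scores are both outcome and covariate, with the visit unstated. If the 18-month scores enter and are partly a consequence of speech, the partial correlation falls from an assumed 0.50 to 0.42-0.38 and approximate power at 27 infants from 0.69 to 0.52-0.43, with the printed slope unchanged. Leaving out age at repair moves the association by 0 to about 0.16 when its correlations with anatomy and speech are each assumed to lie between 0 and 0.4. It is the more clearly grounded of the two omissions, because the document itself links timing to oral stops. The change is worth making and is cheap; the evidence does not support calling the planned analysis invalid.

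**What to change.** 1. State which visit's scores enter the Aim 2 model. If developmental adjustment is wanted in the main analysis, use the presurgical questionnaire and inventory scores. Keep the 18-month scores as secondary outcomes and show the model adjusted for them only as a sensitivity analysis.
2. Add age at repair, as a continuous variable, to the main model.
3. Report the procedure effect again with presurgical cleft width added, as a sensitivity analysis.

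The cost is a change of wording. The repair date, presurgical scans and both rounds of questionnaires are already collected, and the Results section reports 8 infants enrolled and no analysis begun. Each added covariate takes about one degree of freedom. Age at repair added with presurgical scores in place of the 18-month ones costs one net, leaving 17-18 at n = 27. If the scores are dropped from the main model altogether, the change frees one net.

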## Results

This study was funded in August 2024 by the National Institute on Deafness and Other Communication Disorders (R21DC021799). Recruitment and data collection for this study began in April 2025 and are currently underway. As of April 4, 2026, a total of 8 participants have been enrolled, and data analysis has not begun. It is anticipated that enrollment will be complete and final results will be disseminated by the end of 2027 following completion of data analysis.

## Discussion

### Expected Findings

This pilot study will explore the relationship between patient-specific anatomy before and after palate repair and early speech outcomes. Modern attempts to report quantitative measures of the velopharynx in infants have investigated its anatomy [30,46,47] and physiology [20,34,35,48] independently of one another and have commonly used a cross-sectional study design rather than comparing these variables within the same individual over time. Multidimensional data that encompass measures of both anatomy and physiology within the same individual over time are essential for examining how primary palatoplasty affects velopharyngeal form and function at the level of the individual patient. Individualized presurgical planning and responses to surgical treatment are essential for translating basic science findings into valuable patient-specific intervention protocols. This proposal has been designed to take this important step to facilitate precision medicine in this population. Preliminary, data-driven criteria for individualized surgical planning and targeted speech monitoring will be established as a result of this work. Pending a larger, multisite investigation, this work may have future implications to improve and individualize surgical interventions for primary palatoplasty.

Aim 1 will determine which anatomical variables from those used in previous investigations [30,46] can predict the type of surgery received, quantifying the surgical decision-making process objectively using MRI and reducing reliance on surgeon experience to make this decision. We hypothesize that certain anatomical parameters, namely, palatal width and LVP muscle length (Figure 2), may be predictive of surgical procedure selection. If this is the case, this study will provide a quantified, anatomical basis for individualized surgical interventions to support successful palatoplasty and potentially reduce VPI. Alternatively, if there is no anatomical link between patient-specific, presurgical anatomy and surgical decision-making, a more complex, multidimensional analysis of surgical decision-making factors is warranted to improve outcomes of primary palatoplasty and subsequent rates of VPI.

**Figure 2 figure2:**
[figure not shown]
Presurgical magnetic resonance image of an infant labeled with cleft palate with cleft width (A) and levator veli palatini (LVP) muscle length (B).

Through aim 2, we will compare velopharyngeal function for speech among infants with repaired cleft palate following different repair techniques using both perceptual (oral stop production) and objective (anatomical) measures of the velopharynx [29,31]. Given that surgery is an anatomical solution to a physiological concern (aberrant speech), it is essential to establish a link between anatomy and physiology in infants and toddlers to facilitate early diagnosis and remediation of VPI in this population. We further hypothesize that anatomical parameters such as a longer velum, greater effective velopharyngeal ratio, and continuity of the LVP muscle (Figure 3) may be associated with greater diversity of oral stop consonants by 18 months. If this hypothesis is accurate, postoperative anatomy of children with repaired cleft palate could be used as a complement for speech production when it comes to considering secondary surgical intervention. Identifying the relationship between postoperative anatomy and velopharyngeal function in toddlers offers a critical opportunity to intervene earlier and improve speech outcomes in this population. These multidimensional data may provide additional confidence in referring for secondary surgical intervention at an earlier age, when speech production is more limited in clinical visits.

**Figure 3 figure3:**
[figure not shown]
Magnetic resonance image of a typically developing toddler demonstrating the anatomy of interest when considering the risk of velopharyngeal insufficiency. LVP: levator veli palatini.

It is well established that anatomical dimensions have a direct impact on adequate function of the velopharyngeal mechanism for typical speech production. This research will yield promising patient-specific criteria for surgical planning and the success of cleft repair, facilitating earlier and potentially reduced diagnosis of VPI by translating a highly innovative area of research to infants and improving the clinical feasibility of these procedures for VPI diagnosis. We will track participants beyond the 6-month period of this study through their annual cleft team visits to document which children are clinically diagnosed with VPI, measuring the sensitivity and specificity of MRI at 18 months compared to the current clinical paradigm. By applying anatomical findings associated with VPI in older children to infants and toddlers, we may be able to identify VPI risk 3 years earlier than the current clinical paradigm allows. Furthermore, this research addresses a critical gap by assessing surgical outcomes quantitatively rather than perceptually, thus reducing subjectivity and bias. Results may improve the clinical utility of MRI in the surgical planning and monitoring of individuals with cleft palate. These foundational findings may provide support for a forthcoming clinical trial to prospectively match patients with surgical techniques and monitor their outcomes.

Sedation of children for MRI is the typical standard of care worldwide, especially in children under 8 years of age. There is, however, a link between increased anesthetic events in childhood and suboptimal cognitive development [49]. Current imaging methods for children with VPI either are invasive (eg, nasendoscopy) or expose them to ionizing radiation (eg, videofluoroscopy [22,50]). Additionally, children below the age of 3 years are not typically candidates for either procedure due to compliance [22,23]. Nonsedated MRI of the velopharynx avoids these common imaging pitfalls while yielding better rates of patient acceptance and success and greater cost efficiency [50].

Findings will be disseminated through peer-reviewed publications and conference presentations. Any modifications to this protocol will be published along with the findings.

